**Fig. 1 Fig1:**
[figure not shown]
CONSORT flow chart

#### Perioperative measurements

Surgical time, rate of complications, position of the femoral and acetabular components and length of hospital stay will be recorded. Position of the femoral and acetabular components will be measured on an anterioposterior (AP) pelvic X-ray. Inclination of the acetabular component will be measured by defining the angle between the tear drop line and the cup. The version of the cup will be measured by using the method described by Lewinnek et al. [22]. Both the cup version and inclination have been proven to have a high inter- and intraobserver reliability and have been proven to be a reliable and valid method when compared to the gold standard. [23–25] Varus and valgus alignment of the stem will be measured by taking the angle between the femoral shaft and the prosthetic component [26]. These measurements will be performed by KR and an independent orthopaedic surgeon. Measurements will be performed on standard outpatient visits six weeks and one year postoperatively. Additionally, amount of blood loss will be calculated from the drop in postoperative blood hematocrit levels, according to the formula of Nadler et al. [27].

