#### Economic evaluation

An economic evaluation will be conducted to gain insight into cost-effectiveness of the anterior approach compared to the posterolateral approach for THA. After completion of the data collection, the health status, as determined by means of the EQ-5D, will be related to costs in additional economic analyses. These analyses will provide information on the probable cost-effectiveness of the anterior approach compared to the posterolateral approach for THA in the Dutch healthcare system.

The evaluation will be performed from a societal perspective; costs within and outside the healthcare sector will be included. Costs will be registered prospectively, i.e. within the framework of the current study, for all the included patients. A standardised questionnaire on medical costs after THA will be administered at two and six weeks, three months and one year postoperatively. The questionnaire is set up by the Medical Technology Assessment (MTA) and is used in the cost-effectiveness analyses. It contains 11 questions on indirect medical and non-medical issues regarding the THA outside of the hospital. Medical questions include hospital readmissions, visits to the hospital and/or other (paramedical) healthcare workers. Non-medical questions concern patients’ living and working situation.

The direct medical costs, such as the use of the operative theatre, hospital admission and additional interventions (e.g. blood transfusions) will be compared between the two approaches. Most salient cost advantages of the anterior approach are expected in the area of hospitalization costs. Of the various nonmedical costs, informal care costs are assumed to be substantial in the targeted population and will be registered in detail (e.g. visits to the general practitioner, physical therapy). In order to facilitate comparisons with other economic evaluations, unit prices (i.e. the price of one unit of each included cost type) are based on Dutch standard prices [49]. True costs of used resources will be estimated when standard prices are not available.

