### Statistical analysis

To analyse the data SPSS (Statistical Package for the Social Sciences, Chicago, Illinois) will be used. A *p*-value of < .05 will be considered to indicate statistical significance. Descriptive statistics (means and standard deviations) will be used to describe the subject characteristics and the results of the groups. The PASS score is determined by assessing the score on the HOOS of patients who are satisfied with their actual physical state and symptoms. PASS scores will be determined for the measurements made at six weeks, three months and one year postoperatively. The satisfaction question, which is asked on a four-response Likert scale, will be dichotomized into “satisfied” (i.e. the patients who are “very satisfied” or “somewhat satisfied”) and “unsatisfied” (i.e. the patients who are “somewhat dissatisfied” or “very dissatisfied”) [30, 32]. This dichotomized variable will then be used as anchor to calculate cut-off values on the HOOS to determine the PASS score. Next, a ROC analysis will be conducted, using the satisified/dissatisfied variable as anchor. As optimal cut-off value will be the one that maximizes the sum of sensitivity and specificity [30].

After that, all patients will be categorized as responders (i.e. a score on the HOOS beyond the PASS score) and non-responders. Chi-square tests will be used to determine potential differences in the proportion of responders between the study and control group at the above-stated time-points. Additionally, odds ratios with corresponding 95% confidence interval (CI) will be calculated. This ratio represents the odds of being a “responder” for the study group, compared to the control group. An odds ratio larger than 1 favours the study group and the point estimate of the odds ratio is considered to be statistically significant if the 95% CI does not include the value of 1.

Changes in physical activity, participation and gait function will be analyzed with Generalized Estimating Equations (GEE) analyses [51]. Analysis of Variance (ANOVA) will be used to assess differences in urine incontinence (ICIQ-SF), radiographic measurements, surgical time, blood loss and length of hospital stay between the study and control group. Differences in complication rates will be assessed by means of a Chi-square test.

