## Discussion

THA can be performed through several different approaches to the hip joint. These approaches include the anterior, anterolateral, direct lateral, transtrochanteric, posterolateral, and posterior approach. The posterolateral approach is the most commonly used approach [53].

In the last decade minimal invasive surgery techniques for THA have been introduced with the goal of reducing tissue trauma, shorten the length of hospital stay and enhance faster recovery. In the literature minimally invasive techniques are described by an incision that is less than 10 cm in length. However, some of these techniques still cause tissue damage because of soft-tissue dissection [5]. The direct anterior approach on the other hand is a tissue-sparing approach in which intermuscular planes are used to get to the hip joint. Theoretically the anterior approach should result in less tissue damage when compared to the posterolateral approach in which several of the muscles are being dissected. Additionally, because the pelvic musculature remains undisturbed with the anterior approach, it should result in a faster postoperative recovery.

Opponents of the anterior approach claim that it is a more technically demanding approach, which results in a longer operative time, more blood loss and an increase in complications during surgery [54–56]. Moreover, it is said that the anterior approach has a long learning curve, ranging from 20 up to 100 patients [18–21]. However, with more experience a decrease in blood loss, operative time and number of complications is to be expected [19–21]. In the current study all three orthopaedic surgeons are far beyond their learning curve.

The importance of the pelvic musculature in THA patients has been shown in a study by Pfirrmann et al. [15]. In their MRI study they found that patients with persistent symptoms of the operated joint had more defects of the gluteal musculature. Bremer et al. found that the direct anterior approach resulted in less soft-tissue damage to the abductors on MR images, compared to the transgluteal approach [57]. Moreover, Mayr et al. found that the gait function improved in the direct anterior group in the direct postoperative period [12]. Lugade et al. found comparable results [58]. These findings suggest that the direct anterior approach results in a faster recovery. However, these promising results are contradicted in other studies [59, 60].

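### The blood-loss calculation states no term for transfused red cells, so it understates loss in patients sampled after transfusion and can shrink a true difference between the approaches

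*Protocol article*

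**What the plan says.** Under Perioperative measurements, the protocol article states that the "amount of blood loss will be calculated from the drop in postoperative blood hematocrit levels", using a cited published formula. The hematocrit drop is the only patient-level input that the sentence names. It gives no time for the postoperative sample and does not mention transfused volume.

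The Economic evaluation section lists direct medical costs. It states that "additional interventions (e.g. blood transfusions) will be compared between the two approaches", so the trial foresees transfusions and intends to capture their use. It does not link them to the blood-loss measure.

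The Statistical analysis section assigns ANOVA to a group of outcomes that includes "surgical time, blood loss and length of hospital stay between the study and control group". No allowance for transfusion is mentioned there either.

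The Discussion explains why blood loss is of interest. Opponents of the anterior approach are reported to say that it "results in a longer operative time, more blood loss and an increase in complications during surgery". The article replies that these problems lessen with experience and that its surgeons are past their learning curve.

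**The concern.** Transfused red cells raise the hematocrit. If the postoperative sample is drawn after a transfusion, the measured drop is smaller than the bleeding alone would have produced, and so is the loss calculated from it. The error does not fall at random. Transfusion generally follows heavy bleeding, so the understatement is concentrated in the patients with the largest losses.

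What is at stake is a named secondary comparison that bears on a known objection to the trial's intervention. If one approach does cause more bleeding and therefore more transfusion, the rule removes part of that excess from the record, and a real difference may look reassuringly small.

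**Working it through.** **Plan's own figures.** The protocol article gives no mean or SD for blood loss, and no transfusion rate, trigger or volume. There is no figure to reproduce, and every input below is an assumption unless a source is named.

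**1. Loss hidden per unit.** If loss is blood volume × (hematocrit drop) / preoperative hematocrit, a unit given before the sample hides (red-cell volume) / (preoperative hematocrit). With an assumed hematocrit of 0.42:
- 0.15 / 0.42 = 0.36 L
- 0.20 / 0.42 = 0.48 L

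If the formula divides by the mean of the two hematocrits instead (assumed 0.33 to 0.40), the range is 150 / 0.40 = 375 mL to 200 / 0.33 = 606 mL. The order of magnitude does not depend on this choice.

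**2. One illustrative patient.** Assume a blood volume of 5.0 L, a preoperative hematocrit of 0.42, a hematocrit of 0.25 after bleeding, and then two units of 0.18 L red cells.
- True loss: 5.0 × (0.42 − 0.25) / 0.42 = 2.02 L
- Hematocrit after transfusion: 0.25 + 0.36 / 5.0 = 0.322
- Loss by the stated rule: 5.0 × (0.42 − 0.322) / 0.42 = 1.17 L
- Hidden: 0.36 / 0.42 = 0.857 L, which is 42% of the true loss

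**3. Effect on the arm means.** If 5 to 10 percentage points more patients in one arm receive two such units before sampling, that arm's mean is lowered relative to the other by:
- 0.05 × 857 = 43 mL
- 0.10 × 857 = 86 mL

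For scale, assume an SD of 500 mL and 117 patients per arm (half of the planned 260, less the expected 10% loss). The standard error of the difference is then 500 × √(2/117) = 65 mL.

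**4. Simulation in which transfusion follows bleeding.** Assumed inputs:
- mean blood volume 4.8 L and mean baseline hematocrit 0.41;
- mean loss 1,200 mL in one arm and 1,000, 1,200 or 1,400 mL in the other, SD 450 mL;
- 170 mL red cells per unit, with one or two units given when hematocrit falls below 0.24, 0.27 or 0.30. These thresholds only generate different transfusion rates and carry no clinical recommendation;
- recorded loss = blood volume × (hematocrit before − hematocrit after) / mean hematocrit, with the second sample always taken after transfusion.

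With equal true loss and equal transfusion, the recorded difference was about 0 in every setting. With a true difference of 200 mL in either direction, the recorded difference was:

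| Patients transfused | One unit | Two units |
|---|---|---|
| about 2–5% | 186–193 mL | 174–187 mL |
| about 7–17% | 159–175 mL | 123–152 mL |
| about 19–43% | 124–141 mL | 55–87 mL |

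The amount lost from the 200 mL is therefore 7–26 mL, 25–77 mL and 59–145 mL in the three rows. The sign never changed.

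At about 11% transfused, the transfused patients had a true mean loss of 1,941 mL. It was recorded as 1,323 mL with one unit and 772 mL with two. The two-unit figure is below the 1,112 mL mean of untransfused patients, but the one-unit figure is not.

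**The case against.** The strongest reply is that this is a condensed article. Sample timing and the handling of transfused units are working details that may be settled in the full protocol or analysis plan, and the cited formula cannot be inspected here. A sample drawn before transfusion fits the text as well as one drawn after it, and with such samples the mechanism does not operate. This limits how firmly the error can be asserted. It does not remove the point, because the article states a calculation and foresees transfusion, and the calculation as stated gives too low a value for anyone sampled after transfusion.

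The sizes rest wholly on assumptions. That is correct: at the low end, the 43 mL shift is smaller than the assumed standard error of 65 mL, and with rare transfusion the effect is slight.

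A reader might draw three stronger conclusions that the documents do not support:
- **That the comparison between arms is distorted as a matter of fact.** This needs both sampling after transfusion and unequal transfusion, and neither is documented.
- **That the protocol expects transfusion to differ between approaches.** The Economic evaluation section only says that it will be compared; the main cost advantage it expects is in hospitalization.
- **That the bias could reverse the result in favour of the arm that bleeds more.** The simulation showed attenuation only.

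The objection that blood loss is secondary also stands. PASS does not use calculated blood loss, and neither does the cost-effectiveness ratio.

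**Conclusion.** The point holds as a minor one. The stated rule understates blood loss in any patient whose hematocrit is drawn after transfusion, by about 0.36 to 0.48 L per unit under the assumed 0.15 to 0.20 L of red cells and preoperative hematocrit of 0.42. That the understatement occurs follows from red-cell mass balance; its frequency in this trial is unknown.

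For the ANOVA comparison, the consequence is conditional. If true bleeding and hence transfusion differ between arms, the recorded difference can be attenuated towards zero. Under the simulation's assumptions, a true 200 mL becomes 174–193 mL when transfusion is rare (about 2–5%) and 55–141 mL when it is common (about 19–43%). If bleeding and transfusion are equal, the mean difference is unbiased. The PASS conclusion does not change in any of these cases.

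**What to change.** In Perioperative measurements, state that the red-cell volume transfused up to the postoperative hematocrit sample is added to the calculated loss. Fix the same sample time in both arms, and report by arm the number of patients transfused and the units given.

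The addition should be made on the red-cell scale before converting to whole blood. In the patient above, 5.0 × (0.42 − 0.322) = 0.49 L of red cells, plus 0.36 L transfused, gives 0.85 L, and 0.85 / 0.42 = 2.02 L, which recovers the true loss. Adding 0.36 L directly to 1.17 L would give only 1.53 L.

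Using the last hematocrit before any transfusion is not a suitable main rule, because it misses bleeding after that sample and can itself understate loss in heavy bleeders.

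The cost is small but not nil. Units and their timing relative to the sample must be extracted from hospital records, and a standard red-cell volume per unit must be fixed in advance. Transfusion use is already to be captured for the cost analysis, although the article does not show that timing and volume are. No patient procedure changes.

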#### Physical functioning and health-related quality of life

Main study parameter is the Patient Acceptable Symptom State (PASS), which is an approach to measure patient’s responses to treatment. The concept of PASS is based on wellbeing or satisfaction with the actual symptoms and is defined as the value on a patient-reported outcome measure (PROM) beyond which patients consider themselves well [28, 29]. The use of PASS is therefore a simple way to determine whether a patient has achieved therapeutic success. PROMs estimate the effectiveness of healthcare delivered to patients as perceived by the patients themselves. The PASS score is determined by assessing the score on a PROM of patients who are satisfied with their actual physical state and symptoms. Based on patients’ satisfaction with symptoms, the optimal cut-off value of the used PROM can be determined [30–32]. In this study, PASS scores will be derived from scores on the Hip disabilities and Osteoarthritis Outcome Score (HOOS) [33], and they will be determined for the measurements made at two and six weeks, three months and one year postoperatively. The HOOS consists of 5 subscales; pain, other symptoms, function in daily living, function in sport and recreation, and hip-related quality of life. The last week is taken into consideration when answering the questions. The Dutch version of the HOOS is considered valid and reliable [33]. Additionally, the patients’ opinion about “actual satisfaction with their symptoms regarding their hip problem” will be asked with one question. This question will be “if you spend the rest of your life with the hip symptoms you have now, how would you feel?” A Likert version of this question will be used with four response levels: very satisfied, somewhat satisfied, somewhat dissatisfied and very dissatisfied [29, 30, 32]. The scores on this question are then used to calculate PASS. The PASS scores at the previous mentioned time points will each be compared with the preoperative state and then compared between the two approaches [30].

The EuroQol questionnaire (EQ-5D) will also be administered. The health outcomes of the two approaches for THA will be assessed in terms of quality adjusted life years (QALYs). This reflects any differences in health-related quality of life based on the patients’ responses to the EQ-5D questionnaire preoperatively and at up to three points after hospital discharge (six weeks, three months and one year postoperatively). The EQ-5D is a generic questionnaire and consists of 5 questions regarding health-related quality of life [34]. The EQ-5D will also be used as a preference-based measure of health status for the cost-effectiveness analysis [35].

Next to the previous mentioned questionnaires the global rating of change will be assessed [36]. A global rating of change is a single item with which the overall (global) perceived improvement in physical functioning following THA can be assessed. This question is scored on a 7-point likert scale (1 = completely recovered; 2 = much improved; 3 = slightly improved; 4 = not changed; 5 = slightly deteriorated; 6 = much deteriorated; 7 = worse than ever), and asks for the change in physical functioning following THA.

The International Consultation of Incontinence Questionnaire-Short Form (ICIQ-SF) will be administered to evaluate whether THA has influence on urine incontinence [37]. The ICIQ-SF is a subjective questionnaire and is a recommended method to assess the grade of urine incontinence [38]. It consists of four questions on the frequency and volume of urine incontinence and its influence on daily life [37]. With the posterolateral approach the short external rotators of the hip are detached of the greater trochanter. Since the obturator internus muscle is connected to the pelvic floor musculature detachment of this muscle may have a negative effect to urine continence [39, 40], whereas with the anterior approach the pelvic floor remains undisturbed.

Physical activity behaviour will be assessed by means of the International Physical Activity Questionnaire (IPAQ) [41]. IPAQ consists of 27 items which are pre-structured into five subcategories: 1) job-related physical activity; 2) transportation-related physical activity; 3) housework, house maintenance, and caring for family; 4) recreation, sports and leisure-time physical activity; and 5) time spent sitting. The IPAQ records the activity of four intensity levels: 1) vigorous-intensity activity such as aerobics, 2) moderate-intensity activity such as leisure cycling, 3) walking, and 4) sitting. The Dutch version of the IPAQ is considered valid and reliable [42].

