### Measurements

Measurements will be performed by an independent investigator. Standard measurement will take place preoperatively, and six weeks, three months and one year postoperatively. As it is hypothesised that the anterior approach is superior to the posterolateral approach in terms of a faster recovery, mainly in the early recovery period (shorter hospital stay, faster return to normal ADL functioning), extra measurements of physical function, gait analysis and economic evaluation will take place two weeks postoperatively. The questionnaire will be sent to the patients a few days prior to the visit or – when patient do not have an email – will be filled in during the clinical outpatient visit. The filling in of the questionnaire will approximately take 30 to 45 min of patients’ time. A CONSORT flow chart is provided in Fig. 1. Demographic data, preoperative diagnosis, height, weight and Body Mass Index (BMI), ASA classification and the Kellgren and Lawrence (KL) score will be recorded preoperatively.

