For both the study and control group the mean costs, mean effects (measured with HOOS) and mean QALY (based on the utility scores of the EQ-5D) will be calculated. Next, mean costs, mean effects and mean QALYs are used to calculate the incremental costeffectiveness ratio (ICER) [52] by dividing the difference in costs by the difference in effects/QALYs between the study and control group. Uncertainty surrounding the calculated ICER will be examined by the bootstrap method. Incremental cost-effectiveness ratios will be calculated for each of the bootstrap iterations (5000 in the present study), which then will be combined to form a mean ICER with corresponding 95% CI.

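### The EQ-5D schedule as listed has no two-week point, so the QALY-based ICER under-counts any early between-arm advantage; the schedule statements need reconciling

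*Protocol article*

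**What the plan says.** The section on physical functioning and health-related quality of life gives the EQ-5D its own schedule: "preoperatively and at up to three points after hospital discharge (six weeks, three months and one year postoperatively"). The Statistical analysis section makes these utilities the source of the QALY: for each arm, "mean QALY (based on the utility scores of the EQ-5D) will be calculated", and the difference in QALYs is one of two denominators planned for the ICER. The other is the HOOS.

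Other sections treat two weeks as important. Measurements expects the anterior approach to be "superior to the posterolateral approach in terms of a faster recovery, mainly in the early recovery period", and for that reason "extra measurements of physical function, gait analysis and economic evaluation will take place two weeks postoperatively". Under Economic evaluation, the cost questionnaire "will be administered at two and six weeks, three months and one year postoperatively". For the PASS scores derived from the HOOS, "they will be determined for the measurements made at two and six weeks, three months and one year postoperatively".

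No section explicitly places the EQ-5D at two weeks.

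**The concern.** The trial adds a two-week contact to catch an early difference. As the schedules are written, the cost side of the economic evaluation is observed at that contact and the utility side is not. The first utility after surgery comes at six weeks, when part or all of a faster recovery may already have been matched by the other arm.

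What is at stake is the sensitivity of one secondary result, the cost per QALY. If the arms converge by three months, most of any QALY difference arises in the first weeks. The denominator of the ratio is then small, and a modest loss from it can move the ratio a good deal.

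**Working it through.** The article states no QALY figure, so there is none to reproduce. The check compares the listed schedule with the same schedule plus a two-week point.

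**Inputs from the article**
- EQ-5D: before surgery, six weeks, three months, one year (Physical functioning and health-related quality of life).
- Costs: two weeks, six weeks, three months, one year (Economic evaluation).
- QALYs from EQ-5D utilities (Statistical analysis).

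**Assumptions, not in the article**
- Trapezoidal area under the curve, with three months taken as 13 weeks and one year as 52.
- Between-arm utility difference of zero before surgery, at three months and at one year.
- Difference d2 at two weeks of 0.05 to 0.20, and d6 at six weeks of 0 to 0.05 or half of d2.

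**Listed schedule (0, 6, 13, 52 weeks)**

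Incremental QALY = (6 × d6/2 + 7 × d6/2)/52 = 6.5 × d6/52 = 0.125 × d6. The two-week difference d2 does not appear.

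**With a two-week point (0, 2, 6, 13, 52 weeks)**

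Incremental QALY = (2 × d2/2 + 4 × (d2 + d6)/2 + 7 × d6/2)/52 = (3 × d2 + 5.5 × d6)/52.

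**Amount missed**

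(3 × d2 − d6)/52 = (3/52) × (d2 − d6/3), about 0.058 × (d2 − d6/3). The listed schedule under-counts whenever the two-week advantage exceeds one third of the six-week advantage.

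| d2 | d6 | Listed schedule | With two-week point | Missed |
|---|---|---|---|---|
| 0.05 | 0 | 0 | 0.0029 | 0.0029 |
| 0.10 | 0 | 0 | 0.0058 | 0.0058 |
| 0.20 | 0 | 0 | 0.0115 | 0.0115 |
| 0.10 | 0.05 | 0.0063 | 0.0111 | 0.0048 |
| 0.20 | 0.05 | 0.0063 | 0.0168 | 0.0106 |

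**Half the advantage left at six weeks, none at three months (d6 = d2/2)**

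- With the two-week point: (3 + 2.75) × d2/52 = 5.75 × d2/52 = 0.1106 × d2.
- Listed schedule: 3.25 × d2/52 = 0.0625 × d2.
- Share missed: (5.75 − 3.25)/5.75 = 2.5/5.75, about 43%, whatever the size of d2.

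**A dip common to both arms**

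Take illustrative utilities of 0.50, 0.45, 0.75, 0.80 and 0.85 at the five points. The five-point area is 0.7875 and the four-point area 0.7952, an overstatement of 0.0077. If both arms follow this course, the overstatement is the same in each and cancels in the difference. Only an early difference between the arms is affected.

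**The case against.** **The EQ-5D may be intended at two weeks.** Measurements places economic evaluation there, and the Economic evaluation section describes that evaluation as relating EQ-5D health status to costs. The abstract says that quality of life is assessed by questionnaire and gives a general schedule that includes two weeks. This stands as a possible reading. Against it, the EQ-5D has its own explicit list. The Participation section likewise gives its questionnaire a list without two weeks, so the abstract's general schedule does not apply to every instrument. The outcome is an inconsistency to resolve, not proof of a deliberate omission.

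**No interpolation method is stated.** Correct, and an article may leave this to the fuller documents. The exact figures depend on the trapezoid. The gap does not: any method must cross from surgery to six weeks without an observed utility.

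**The amounts are small.** With an assumed one-year QALY standard deviation of 0.10 to 0.20 and 120 patients per arm, the standard error of the difference is SD × √(2/120), or 0.013 to 0.026. Even the largest missed amount in the table is below one standard error. This stands, and it keeps the point at the level of a cheap improvement.

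**Stronger readings.** A reader might infer that an early gain cannot enter the QALY at all. That holds only if it has closed by six weeks; in the half-remaining case 57% is still captured. A reader might also infer that the whole cost-effectiveness answer is tilted. The article does not support this. The HOOS-based ratio does not use the EQ-5D, and the under-count arises only if there is an early between-arm difference. If the anterior approach is better early, the gap works against it, so it could not produce a false claim of benefit. If it were worse early, the gap would hide part of that.

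**Conclusion.** The point holds in a limited form. As listed, the EQ-5D schedule is insensitive to the early difference that the trial expects, and it does not sit well with the two-week economic evaluation. The loss is 0.003 to 0.012 QALY if an advantage of 0.05 to 0.20 at two weeks has closed by six weeks, and about 43% of the gain if half remains at six weeks and it closes by three months. These sizes rest on the trapezoid, equal baselines and utility differences that the article does not give.

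Only the QALY-based ICER is concerned. The primary PASS outcome, the sample size built on it, the HOOS-based ICER and the early cost data are untouched.

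**What to change.** First reconcile the EQ-5D list in the section on physical functioning and health-related quality of life with the abstract and with the two-week economic evaluation under Measurements.

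If the EQ-5D is not yet taken at two weeks, add it to that list and to the existing two-week questionnaire, and state that the two-week utility enters the QALY calculation. If it is already taken, correct the list and state the same.

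The cost is five questions at a contact that already takes place, set against a questionnaire that the article puts at 30 to 45 minutes. The downside is a slightly longer two-week form. The change should come early, because a utility not asked for at two weeks cannot be observed afterwards. For patients who have already passed that visit, the gap should be reported as a limitation of the QALY-based ratio.
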